### Informed consent

Written informed consent will be obtained from participants at recruitment, following initial screening using the SRQ-20 and prior to WHODAS 2.0 and CAGE assessment. Informed consent will be obtained by trained health workers, and a copy of the Information Letter and Consent Forms will be provided to participants.

### Confidentiality

All electronic data will be saved on a secure server. The hard copy questionnaires will be stored in a locked cabinet at the CHS or at the project’s head office in Hanoi. Only authorized research team members will have access to hard copy and electronic questionnaires. The hard copy questionnaires and the electronic versions will be saved for 5 years and will then be destroyed, according to Vietnamese requirements. All prescreening data for patients that are not recruited to the study will be stored in a locked cabinet in the CHS, and will be destroyed after 1 year, as is standard practice in Vietnam.

Study participants will be assigned a unique code. This code will be used in the database to ensure confidentiality. No identifying information, such as name or demographic features, will be attributed to specific participants to uphold confidentiality.

### Inclusion and exclusion criteria

Inclusion criteria for the study are: (1) participant meeting caseness based on an SRQ-20 score of >7 and (2) consent of participant to participate and complete all measures. Exclusion criteria are: (1) cognitive disturbance, (2) symptoms of severe mental illness, including psychosis, severe depression and suicidal ideation, (3) visual or hearing impairment such that patients cannot use the manual or work with a care provider and (4) illiteracy. Patients presenting with symptoms of severe mental illness, including severe depression, will be referred to specialist services at the time of screening.

If patients enrolled in the study should become suicidal or experience psychotic symptoms during the study, primary care providers and social workers will be instructed to refer patients to tertiary care. Patients receiving treatment in tertiary care will no longer remain in the study. Every effort will be made to follow up and conduct outcome measures with these patients; however, the severity of their illness and nature of their treatment may make this difficult.

### Intervention

SSM is an approach to chronic illness management that acknowledges the active role of the patient in their own care, taking a collaborative approach in which a patient is supported by a health care provider, peer or family member [12]. In SSM for depression, patients are given a SSM guide that is based on the principles of cognitive behavioral therapy, including behavioral activation, cognitive restructuring, and problem solving [12]. Patients are provided with encouragement and coaching in using the SSM guide. In systematic reviews of SSM in Western contexts, SSM was found to have an effect size that is similar to conventional treatments for depression, such as psychotherapy, and was shown to be more cost-effective than antidepressants or psychotherapy [12]. SSM is also cost-effective for both patients and health systems and can replace unnecessary prescription of antidepressant medications in patients with mild-to-moderate depression [12]. The SSM intervention that is being tested in Vietnam uses the *Antidepressant Skills Workbook* [28], which was developed by mental health specialists at Simon Fraser University. The *Antidepressant Skills Workbook* was validated for its cultural acceptability in Vietnam and was translated and back translated for semantic equivalence during the pilot study.

The intervention training is a course delivered to primary health care workers, social workers and social collaborators (volunteer lay social workers) about depression and SSM that has been culturally adapted for use in Vietnam. Primary health care staff at CHSs, social workers and social collaborators will be provided with enhanced training about depression, which will supplement their minimal mental health training. This includes information about the symptomatology and etiology of depression and evidence about treatment options, including SSM. This training is informed by research about commune health workers’ existing levels of knowledge, training and explanatory models of common mental disorders [27] to ensure that the training is culturally relevant and responsive to health workers’ training and experience. Health and social workers will subsequently be introduced to, and trained in using, the SRQ-20, WHODAS 2.0 and CAGE to identify depression, disability and alcohol use among patients. They will also be trained in using the adapted version of the *Antidepressant Skills Workbook* and in the SSM approach. Following health worker training, patients will be screened when accessing primary care services at the CHS or in the community and recruited into the study. Patients will be provided with the *Antidepressant Skills Workbook* and will be supported in its use by a social worker or social collaborator for 2 months. SRQ-20 and WHODAS 2.0 measures will be taken at baseline, at 1 month, and at 2 months. The SSM intervention is delivered in a short period of time, often over the course of 9–12 weeks [12]. The feasibility study results showed a pattern over the three data points, with depression and functional ability scores improving from baseline to 2 months.

### Control condition

The control condition will be enhanced treatment as usual. For the most part, depression is not recognized or treated in primary care centres in Vietnam and it is, therefore, likely that patients who are receiving primary care at CHSs or who have been screened by social workers in the community in communes that are randomized to the control condition will receive little or no treatment for depression. Enhanced treatment as usual will consist of the following:Health and social workers will receive training that recommends “watchful waiting,” except in severe cases, including suicidal ideation, psychosis and the possibility of causing harm to others. Training will also include information about how to respond to emergency situationsPatients will receive a leaflet adapted from the *Beyond Blue “Understanding Depression”* Leaflet (www.beyondblue.org.au) that provides information about depression, providing patients with information about their diagnosis, including depression symptoms, risks and approaches to treatment

Patients in communes randomized to the control condition will be offered SSM following the period of control data collection, after 4 months. At the time of the 1- and 2-month assessments, we will capture what, if any, additional treatment has been accessed by the patient (e.g., services at the tertiary-care level, informal or formal counseling, supplements, traditional Vietnamese interventions, sleeping pills). Concomitant care is not prohibited during the trial, but the study team will record any formal or informal treatments and services that might be accessed by patients during their enrollment in the study.

### Randomization

Randomization will be done using permuted blocks (to conceal allocation) and will be stratified by district. The randomization sequence will be developed and controlled by an individual ([name] at Simon Fraser University) not otherwise involved in the study to ensure fidelity. Details of the randomization, such as block sizes and software implementation, will be outlined in the Statistical Analysis Plan (SAP) to prevent anticipated allocation of the communes to getting the early or later timing of the SSM intervention. The SAP will be developed after this protocol is submitted for publication; however, the plan is to link them when they are published.

### Blinding

It will not be possible to institute full blinding because of the nature of the intervention. Project outcome assessors will be blinded. Based in the project head office in Hanoi, outcome assessors will conduct the 1- and 2-month assessment interviews with patients by telephone. The outcome assessors will have no information about patients, where they are located or whether they are allocated the intervention or control condition. The project research coordinator will collect telephone numbers from the participants, and will assign them an appointment with the outcome assessor. The outcome assessor will then call the telephone number with no additional information about the participant. Participants will be instructed not to share information about whether they are part of the intervention or control group with outcome assessors to avoid contamination.

### Data collection

Baseline data will be collected by primary care staff, social workers and social collaborators. Outcome assessors will collect follow-up data by telephone at 1 and 2 months. Outcome assessors will receive 3 days of training on the use of the SRQ-20, WHODAS 2.0 and CAGE.

Several strategies are in place to participant retention and to encourage adherence to the study protocols. Patients who participate in visits with social workers every 2 weeks and complete the final outcome evaluation will be provided with a small gift (e.g., hand lotion). The Department of Labor, Invalids and Social Affairs (DOLISA) in each province will also provide a bonus to social workers for their participation in the study.

We will continue to collect data from participants who discontinue their participation in the study by ensuring that we have up-to-date telephone numbers for all participants. As symptoms improve, patients who have been unable to work will likely return to employment. In cases, such as with agricultural laborers, where the nature of their work might prohibit their participation in the study, we will provide additional compensation to these participants to encourage them to complete the outcome assessment.

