**Methods/design:**

The MAC-FI program will be assessed using a stepped-wedge, randomized controlled trial. Study participants are adults aged 18 years and over in eight provinces of Vietnam. Study participants will be screened at primary care centres and in the community by health and social workers using the Self-reporting Questionnaire-20 (SRQ-20). Patients scoring >7, indicating depression caseness, will be invited to participate in the study in either the SSM intervention group or the enhanced treatment as usual control group. Recruited participants will be further assessed using the World Health Organization’s Disability Assessment Scale (WHODAS 2.0) and the Cut-down, Annoyed, Guilty, Eye-opener (CAGE) Questionnaire for alcohol misuse. Intervention-group participants will receive the SSM intervention, delivered with the support of a social worker or social collaborator, for a period of 2 months. Control- group participants will receive treatment as usual and a leaflet with information about depression. SRQ-20, WHODAS 2.0 and CAGE scores will be taken by blinded outcome assessors at baseline, after 1 month and after 2 months. The primary analysis method will be intention-to-treat.

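### The retention gift depends on fortnightly social-worker visits that are described only for SSM patients, so month-2 follow-up could differ by arm and by adherence

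*Protocol article*

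**What the plan says.** The Data collection section introduces its incentives as serving two aims at once: "Several strategies are in place to participant retention and to encourage adherence to the study protocols". The first incentive is the gift: "Patients who participate in visits with social workers every 2 weeks and complete the final outcome evaluation will be provided with a small gift". No arm is named, and the example given is hand lotion.

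The Intervention section says that SSM patients receive the workbook and "will be supported in its use by a social worker or social collaborator for 2 months". The Control condition section opens its definition with "Enhanced treatment as usual will consist of the following" and lists two items: staff training that recommends watchful waiting, and a patient leaflet. The abstract agrees: "group participants will receive treatment as usual and a leaflet with information about depression". The Control condition section also expects that control patients "will receive little or no treatment for depression". No scheduled visits are listed for them.

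On follow-up, the Data collection section says "Outcome assessors will collect follow-up data by telephone at 1 and 2 months". It adds that participants who discontinue will still be followed, with telephone numbers kept current for all. It anticipates that "As symptoms improve, patients who have been unable to work will likely return to employment", and it offers extra compensation for completing the outcome assessment to those whose work gets in the way.

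**The concern.** A retention incentive should act equally on everyone whose outcome is to be compared. This one is joined to a condition that belongs to the experimental treatment. As described, it pulls SSM patients who keep attending towards the final evaluation. It does nothing for SSM patients who have stopped attending, and apparently nothing for controls.

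The primary measure is the proportion moving from case to non-case, compared between arms by intention-to-treat. If completion depends on arm and on adherence, and adherence is related to recovery, the proportion among completers no longer estimates the proportion among all those enrolled. The Analysis section plans mainly multiple imputation when more than 3% is missing. That helps only to the extent that observed data explain who is missing.

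**Working it through.** **1. Who can earn the gift, as written.** Setting the Data collection rule beside the Intervention and Control condition sections:

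| Participant | Fortnightly visits described? | Completes final evaluation | Gift |
|---|---|---|---|
| SSM, attends visits | Social-worker support for 2 months; the interval appears only in the gift rule | Yes | Yes |
| SSM, misses visits | Support offered, not taken up | Yes | No |
| Control | None listed | Yes | Apparently no |

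Controls are offered SSM after 4 months, which is later than their month-2 outcome. A gift earned then cannot support retention in the comparison.

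**2. Size of a possible bias.** The document states no retention rates and no non-case rates by arm, so every rate here is an assumption. Let p be the true non-case proportion, and r1 and r0 the follow-up rates in non-cases and cases. The proportion observed among completers is

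p·r1 / [p·r1 + (1 − p)·r0].

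*No true effect, SSM loses more unrecovered patients.* Take r1 = 95% in SSM, and control follow-up unrelated to outcome, so that the control proportion is observed without bias. For p of 30%, 50% and 70%, the spurious difference in favour of SSM is:
- r0 = 90%: 1.1 to 1.4 points
- r0 = 85%: 2.3 to 2.8 points
- r0 = 75%: 4.7 to 5.9 points
- r0 = 70%: 6.0 to 7.6 points

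For example, with p = 50% and r0 = 85%: 0.475/(0.475 + 0.425) = 0.528, a bias of 2.8 points. Overall SSM follow-up is then 90%. If control follow-up is also 90%, completion by arm looks identical although the bias is present.

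*The reverse.* If the SSM patients who stop visits are the recovered ones who went back to work, swap the rates: r1 = 85%, r0 = 95%, p = 50%. This gives 0.425/(0.425 + 0.475) = 0.472, a bias of 2.8 points against SSM.

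*Loss of recovered patients through work.* Assume true recovery of 60% in controls, and that 15% of recovered and 5% of unrecovered are lost. The observed control rate is 0.51/(0.51 + 0.38) = 57.3%, which is 2.7 points low. With 25% and 5% lost it is 0.45/(0.45 + 0.38) = 54.2%, which is 5.8 points low. Those shifts carry over fully to the difference only if SSM patients are not lost in the same way. Assume 80% recovery in SSM with the same losses. SSM is then observed at 0.68/0.87 = 78.2% and 0.60/0.79 = 75.9%. The observed differences are 20.9 and 21.7 points against a true 20, so the bias falls to about 0.9 and 1.7 points. Only the extra control loss caused by lacking the gift counts as a consequence of the rule.

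**3. Sample size.** The plan's figure reproduces: 64 per arm, 128 in total, times 1.35 = 172.8, or 173. The gift rule does not affect it. Assuming an equal split of the planned 256 (128 per arm), effect size 0.5 and design effect 1.35, power is about 92% with 95% retained in both arms and about 88% with 95% against 75%. The issue is bias, not power.

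**The case against.** The strongest reply is that the document never says that visits are confined to SSM or that controls get no gift. The rule refers to patients without naming an arm, control-arm social workers also receive study training, and this is a condensed article. That stands as a limit: SSM-only visits are a strong inference, not a stated fact. But the control condition is presented as a definition with two items, and the abstract agrees with it. If controls do have fortnightly visits, the Control condition section does not match the gift rule and the two need reconciling.

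A reader might also infer that outcome completion is rewarded in one arm only. That is not supported. The work-related compensation rewards completion of the outcome assessment, is tied neither to an arm nor to visits, and is aimed at the recovered patients one would fear losing. The inference can apply only to the gift.

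A further tempting inference is that the rule inflates the SSM effect. The direction is not established: patients who recover and return to work may be the ones who miss visits, and losing them would lower the SSM proportion.

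Finally, the article lists real safeguards: telephone assessment from a central office by appointment, follow-up of discontinuers, multiple imputation with possible sensitivity analyses, and a month-1 SRQ-20 score that can inform the imputation. Rewarding attendance is also a legitimate adherence aim. All of this reduces the likely size. It does not explain why the reward for completing the outcome should depend on attendance.

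**Conclusion.** The point holds as a modest design weakness. As written, one retention incentive is conditional on intervention contact, is apparently out of reach for controls during the comparison, and is forfeited by non-attending SSM patients. Follow-up could therefore differ by arm and by adherence.

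Any resulting bias in the non-case proportion is of unknown direction and probably small. The range of about 1 to 8 points rests entirely on assumed follow-up gaps of 5 to 25 percentage points between recovered and unrecovered SSM patients. Nothing in the document suggests that so small a gift would by itself produce gaps at the upper end. This is a cheap improvement rather than a flaw that undermines the trial.

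**What to change.** - Give the same gift to every participant in both arms for completing the month-2 telephone assessment, regardless of visit attendance.
- Record the date of the change, so that participants enrolled before and after it can be told apart.
- Report month-2 completion by arm and, within SSM, by visit attendance. Completion by arm alone can look balanced while bias remains.
- If controls do have fortnightly visits, reconcile the Control condition and Data collection sections.

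The cost is a small gift for about 128 controls (half of the planned 256) and for SSM patients who miss visits, an ethics notification, and the loss of a minor adherence incentive. Because recruitment is already underway (Trial status section), participants enrolled before and after the change will have had different incentives. That matters somewhat in a design where calendar period counts, which is why the date should be recorded.

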### Power calculation

The number of subjects required for this randomized cluster trial was calculated by estimating the number that would be required in a completely randomized design and then adjusting this number by the design factor associated with a randomized cluster trial (Table 2). The number of subjects required for a completely randomized design was calculated by the R function pwr.t.test [29] using the following characteristics:An effect size of 0.5 (where a small effect size is 0.2; medium is 0.5; large is 0.8)Significance level – type 1 error rate (0.05)a two-sample design

Using a medium effect size (0.5) results in an estimate of 64 subjects per arm or 128 in total at an 80% power.

**Table 2 Tab2:** Sensitivity analysis

Effect size	ICC	Number per cluster	Total *N* required
0.5	0.05	8	173
0.8	0.05	8	69
0.2	0.05	8	1063
0.3	0.05	8	474
0.4	0.05	8	268
0.45	0.05	8	212
0.5	0.025	8	150
0.5	0.01	8	132
0.5	0.005	8	132
0.45	0.005	8	163

*ICC* intracluster correlation coefficient

The Design Effect (DE) is estimated by the formula:$$ D E = 1 + \left(\mathrm{n} - 1\right) \times \mathrm{p} $$where

*DE* = Design Effect

*n* = number of subjects in each cluster

*p* = ICC (intracluster correlation coefficient)

No estimates of the SRQ-20 intracluster correlation coefficient (ICC) are available; however, within the research literature on estimating sample sizes, the ICC is usually described as small with values of 0.01 to 0.05 – with a median of around 0.01. We have used the upper value of 0.05. This is the number of participants who will be found to have an SRQ-20 > 7 and will be followed up over the 2 months. This was estimated from the feasibility data, which produced approximately one subject every 14 days within primary care centres (or one every 2 weeks). We therefore estimate a mean of eight subjects per commune would be completed in the experimental or control time period, meaning that the total *n* during the study period is 32 clusters × 8 completed subjects per cluster or 256 subjects. The DE associated with eight subjects per cluster, a medium effect size of 0.05, and an ICC of 0.05 is 1.35, meaning that the randomized cluster study requires 128 × 1.35 or 173 subjects which is below the anticipated *n* of 256.

If the expected effect size is under 0.45 the study is likely underpowered. In the feasibility study, nine of the 68 (13%) subjects remained at 8 or higher in the second SRQ-20 – thus, 87% dropped below 8, a very large effect of the intervention. While the effect size in the pilot study would fall into the “large” category the variable follow-up time makes the estimate suspect, and thus we used a medium effect size to account for the expected impact over a 2-month period. Based on the feasibility results of eight patients per cluster, an expected minimum effect size of 0.4, an ICC of no more than 0.05 the proposed study would be powered at approximately 80% with a 0.05 alpha level.

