### Design

The study uses a cluster-randomized, stepped-wedge controlled trial design. Randomization will occur at the commune level and communes will be assigned to receive either the SSM intervention first or the control condition first. The control condition will be enhanced treatment as usual. Those communes assigned to receive the control condition first will receive the SSM intervention 4 months later. This will ensure that the study is conducted ethically and will not deny evidence-based services to members of the control group. Participants in the intervention and control groups will be from different communes, or municipal districts, meaning that they do not access the same service units. This will minimize the risk of contamination. Figure 2 shows how the design will operate. The *black rows* depict the experimental data collection periods, *diagonally striped rows* are the control data collection periods, and the *gray rows* represent the long-term data collection period. The primary measure of interest is the proportion of individuals in the experimental versus the control group (*black* versus *diagonal striped*) that went from being a case of depression (SRQ-20 > 7) to being non-case (SRQ-20 < 8) over the experimental data collection period. Based on the feasibility case rate of a mean of one case every 14 days, each commune is expected to have eight completed cases (baseline, month-1 and month-2 measures) per year for a total *n* of 256 cases. Figure 3 shows a SPIRIT figure depicting the study design. Additional file 1 provides an overview of the elements of the study protocol, as described in a SPIRIT checklist.  Recruitment will continue until the desired sample size is reached and data can be analyzed to assess the effectiveness of the intervention.

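### The anticipated 256 completed cases do not follow from one case per 14 days and the stated time windows; if the 4-month control period includes follow-up, about 70 controls complete, not 128

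*Protocol article*

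**What the plan says.** The Design section states: "Based on the feasibility case rate of a mean of one case every 14 days, each commune is expected to have eight completed cases", where completed means having the baseline, month-1 and month-2 measures, and the period is a year ("eight completed cases (baseline, month-1 and month-2 measures) per year for a total"). The Power calculation section cites the same feasibility rate, "approximately one subject every 14 days within primary care centres (or one every 2 weeks", but ties the eight to a different period: "We therefore estimate a mean of eight subjects per commune would be completed in the experimental or control time period". Both multiply by 32 communes to reach 256, which is then set against a requirement of 173.

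On timing, the Design section says: "Those communes assigned to receive the control condition first will receive the SSM intervention 4 months later". The Control condition section says that control patients "will be offered SSM following the period of control data collection, after 4 months". Outcomes are taken at 1 and 2 months. The Design section adds: "Recruitment will continue until the desired sample size is reached". The section on participants allows extra communes and a longer study if recruitment proves difficult. The Power calculation section ends by claiming approximately 80% power at a minimum effect size of 0.4, with eight patients per cluster and an ICC of no more than 0.05.

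**The concern.** The same eight cases per commune are attached to a year in one section and to the control or experimental period in another, although the control period is 4 months. A participant counts as completed only after 2 months of follow-up, so a 4-month period cannot hold both 16 weeks of enrolment and the follow-up of the last participants enrolled.

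The figure matters because 256 is what makes the trial look comfortably larger than the required 173, and it supports the power claim at 0.4. Control time is also the scarce resource. Once a control-first commune has switched, further recruitment there adds only SSM participants, so a single overall target can be met with a short control arm.

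**Working it through.** **Inputs from the protocol.** Rate: 1 case per 14 days per commune. Communes: 32. Control period: 4 months. Follow-up: 2 months. Effect size 0.5, alpha 0.05, power 80%, ICC 0.05, 8 per cluster.

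**Inputs assumed here.** A two-sided test, which reproduces the plan's 64 per arm; 16 communes starting in each condition; a month of 365.25/12 = 30.44 days.

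**Reproducing the requirement.** A two-sample t-test at 0.5 needs 63.8, so 64 per arm and 128 in total. The design effect is 1 + 7 × 0.05 = 1.35, and 128 × 1.35 = 172.8, which is the stated 173. The requirement is not in dispute.

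**Reproducing the anticipated number.** Completed per commune = (window − follow-up) / 14 days.
- 16 weeks, no follow-up: 112/14 = 8.0; × 32 = 256. This is the only route to 256, and it counts enrolled cases.
- One year, no follow-up: 365.25/14 = 26.1.
- One year less 2 months: 304.4/14 = 21.7.
- Four months less 2 months: 60.9/14 = 4.35; × 32 = 139.
- Conversely, eight per year would mean one case every 365.25/8 = 46 days. Eight completed cases need 112 + 60.9 = 173 days, about 5.7 months.

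**Size of the arms if the 4 months include follow-up.**
- Controls: 16 × 4.35 = about 70, against 16 × 8 = 128.
- Total if the same window limits all communes: about 139.
- Total if only control-first communes are limited: 128 + 70 = about 198.

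**Power.** Each arm's n is divided by its own design effect, 1 + (m − 1) × 0.05, where m is the mean number per commune in that arm. The result goes into a two-sample t-test.

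| Scenario (SSM / control) | Power at 0.5 | Power at 0.4 |
|---|---|---|
| As stated, 128 / 128 | 93% | 78% |
| All communes limited, 70 / 70 | 77% | 58% |
| Only controls limited, 128 / 70 | 85% | 67% |
| SSM recruitment continued to 256, 186 / 70 | 88% | 71% |

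In the second row the design effect is 1 + 3.35 × 0.05 = 1.17 and the requirement at 0.5 is 128 × 1.1675 = about 149, so 139 falls short.

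**If the 4 months are enrolment only.** Eight per commune then fits (121.8/14 = 8.7). With even enrolment, those who enter in months 2 to 4, about half, have their month-2 assessment after their commune has switched to SSM.

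**The case against.** The strongest reply is that 4 months may be the enrolment window, in which case eight per commune is right. The Design section says only that SSM arrives 4 months later, and the figure that lays out the periods is not shown. The Control condition wording points the other way, since it places the offer of SSM after control data collection. It could also mean that each control patient is offered SSM only once that patient's own data are complete. This part stands: the shortfall is conditional on the reading. The alternative reading, however, puts about half of the month-2 control assessments after the commune's switch, so it also needs attention.

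A reader might infer that the trial will have 139 participants and 77% power. The documents do not support that as a firm result. Only control-first communes lose their condition at the switch, and no length is given for the experimental period. If only those communes are limited, power at the planning effect of 0.5 stays above 80%.

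A reader might also infer that the shortfall cannot be repaired. Within the existing communes, recruitment after the switch indeed adds no controls. But the section on participants foresees additional communes, and these could supply controls if randomised with their own control period. The text does not say they would be, and it is a contingency for difficult recruitment, whereas this shortfall arises with recruitment exactly on plan.

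Finally, a reader might calculate a diluted effect under the enrolment-only reading, for example 0.5 × (1 − 0.25) = about 0.38. The 25% is the mean share of SSM exposure over all controls (50% among those who cross). It presumes immediate uptake at the switch and an effect that builds linearly. Neither is in the protocol, so that figure is illustrative at most.

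**Conclusion.** The derivation of 256 is wrong as written. The two sections contradict each other on the period, and no stated window gives eight cases with complete 2-month data. This holds on the protocol's own figures.

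The size depends on the reading of the 4 months. If they include follow-up, about 70 controls complete instead of 128, and the total is about 139 to 198. Power at an ICC of 0.05 is then about 77% to 85% at 0.5 and 58% to 67% at 0.4, or about 71% at 0.4 if SSM recruitment runs on to 256. The claim of approximately 80% at 0.4 is not delivered in any of these cases. At 0.5, 80% is missed only if all communes are limited. If the 4 months are enrolment only, the numbers fit, but the month-2 contrast is exposed to crossover in about half the controls. These figures assume steady accrual at the stated rate, no dropout, and equal numbers of communes starting in each condition.

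**What to change.** 1. Reconcile the yearly figure in the Design section with the per-period figure in the Power calculation section, and state whether the 4 months before the switch include the 2-month follow-up.
2. Restate the expected completed number per commune and per arm from the stated rate, and give the resulting power at 0.5 and 0.4.
3. State the recruitment target per arm, with the control target to be met by participants enrolled before their commune's switch. If communes are added, say whether they are randomised with their own control period.
4. Analyse participants by their commune's status at enrolment, and prespecify a sensitivity analysis that leaves out control month-2 outcomes taken after the switch. The detail can sit in the statistical analysis plan.

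The cost is a change of wording, probably a less favourable stated sample size and power, and one additional analysis. Recruitment is already under way and control time in a switched commune cannot be recovered, so the per-arm target should be settled early.
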